### **9.3.2 Serious Adverse Event (SAE) Definition**

Adverse medical events at any dose as defined by ICH-GCP:

Cause death;

Life threatening;

Requiring hospitalization or prolonged hospitalization;

Resulting in permanent or severe disability/incapacity;

Congenital malformations/birth defects.

### **9.3.3 Adverse event classification**

#### **9.3.3.1 Incident Severity**

Classified according to the Common Terminology Criteria for Adverse Events (CTCAE) version 5.0:

CTCAE provides a specific clinical description of the severity of each adverse event (Grade 1 to 5) based on the following basic guidelines.

Grade 1: Mild; asymptomatic or mild; seen clinically or diagnostically only; no treatment required

Grade 2: Moderate; requires lesser, local or non-invasive treatment; age-appropriate instrumental limitation of activities of daily living.

Grade 3: Severe or medically significant but not immediately life-threatening; results in hospitalization or prolonged hospitalization; disability; autonomic limitation of activities of daily living.

Grade 4: Life-threatening; requires urgent treatment.

Grade 5: Death related to AE.

#### **9.3.3.2 Relevance to Research Interventions**

Classified by determined relevant, possibly relevant, potentially relevant, unlikely relevant, irrelevant.

#### **9.3.3.3 Expectancy**

Adverse events are first identified as expected or unanticipated. If an adverse event is expected it should be collected using a standard format and its expectedness can be assessed based on previous observed adverse events; if the nature, severity, or frequency of the adverse event does not match the risk information described in previous study interventions, it can be considered unanticipated.

#### **9.3.4 Timing, frequency, follow-up, and regression of adverse event assessments**

The nature of the adverse event was determined by combining the definitions of AE and SAE from the ICH-GCP and GCP. All AEs including local and systemic reactions should be collected using a case report form (CRF) that collects information including description of the event, time of occurrence, physician's assessment of severity, relationship to the investigational product, and time to resolution/stabilization of the event. All AEs should be given adequate resolution. At each study follow-up visit, the investigator will ask about AEs/SAEs that have occurred since the

last follow-up visit, and the AE/SAE will be followed until resolved or stabilized.

#### **9.3.5 Adverse Event Reporting**

Describe the AE reporting process, including timeframes, according to relevant guidelines.

#### **9.3.6 Serious Adverse Event Reporting**

Describe SAE reporting procedures, including timeframes, according to relevant guidelines.

The investigator will immediately report any SAE to the sponsor, whether or not it is related to the study intervention.

#### **9.3.7 Reporting adverse events to study subjects**

The information would be shared with subjects.

### **9.4 Unexpected problem**

#### **9.4.1 Definition of Unexpected Problems**

Unexpected problems include events, experiences, or outcomes in which the study subjects meet the following criteria:

- 1) The problem is unintended in nature, severity, and frequency based on the study protocol, informed consent form, and characteristics of the study subject.
- 2) The study participant is at a more serious risk than previously recognized events, experiences, or outcomes that meet the definition of an unintended problem that should be guaranteed to be changed to protect the safety, welfare, or rights of the subjects.

Actions taken include:

- 1) Modifying inclusion and exclusion criteria to reduce newly identified risks
- 2) Implementation of additional safety monitoring procedures
- 3) Suspending recruitment of new subjects or discontinuing study procedures
- 4) Modifying the informed consent form to include a description of newly identified risks
- 5) Providing additional information on newly identified risks to subjects already enrolled in the study

#### **9.4.2 Reporting of unexpected problems**

Unanticipated problems should be reported as soon as possible and their reporting procedures described, including time frames.

Include the following information:

- 1) Detailed description of the event, experience, and ending
- 2) Explanation of the decision that the event, experience, or ending is an unintended problem
- 3) Actions to be taken to deal with the problem

## **10. Statistical analysis**

### **10.1 General method**

Random numbers were generated by computer. SPSS software (version 23) was used for data statistics, and PASS software (version 11.0) was used for sample size calculation. In descriptive statistics, data were expressed in the form of frequency (percentages) for categorical variables and medians (interquartile) or means  $\pm$  standard deviations (SD) for continuous variables. In addition, t-tests were used to compare between-group differences in continuous variables after

exploring the normality of data distribution using the Shapiro-Wilk test. Mann-Whitney U tests were used to compare continuous variables with a skewed distribution. Pearson Chi-square or Fisher's exact tests were used to compare between-group differences in categorical variables. All tests were performed two-sided at the significance level of 5%.

## **10.2 Analysis of primary and secondary research endpoints**

In descriptive statistics, data were expressed in the form of frequency (percentages) for categorical variables and medians (interquartile) or means  $\pm$  standard deviations (SD) for continuous variables. In addition, t-tests were used to compare between-group differences in continuous variables after exploring the normality of data distribution using the Shapiro-Wilk test. Mann-Whitney U tests were used to compare continuous variables with a skewed distribution. Pearson Chi-square or Fisher's exact tests were used to compare between-group differences in categorical variables. Relative risk (RR) was used to compare the proportion of patients with the endpoint between the MMF and Control groups. We estimated the severe flare-free survival proportion of the MMF group and Control group using the Kaplan-Meier method with a log rank test. For the primary outcome assessed at two levels (mild-to-moderate and severe flares), Bonferroni correction was used and two-sided at a significance level of 0.025. Other tests were performed two-sided at the significance level of 0.05.

## **10.3 Security Analysis**

AEs are coded and calculated and may be expressed using severity, frequency, and association with the intervention. Adverse events leading to discontinuation of the research intervention and serious AEs resulting from treatment should be listed individually.

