### **7.1.4 Items and times of clinical and laboratory examinations to be carried out**

Patients were observed for clinical manifestations, assessment of disease condition, detection of liver and kidney function, erythrocyte sedimentation rate (ESR), CRP, blood and urine routine, anti-dsDNA antibody levels, complement C3, C4, immunoglobulin, SLEDAI-2K score, SF-36 score, medication use, and adverse reaction (AEs) records.

Number of visits: at screening + 4 follow-up visits (week 24, 48, 72, 96).

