### 7.4 Follow-up and compliance

During the study, the patients were followed up for 4 times (week 24, week 48, week 72, week 96). Patients were observed for clinical manifestations, assessment of disease condition, detection of liver and kidney function, erythrocyte sedimentation rate (ESR), CRP, blood and urine routine, anti-dsDNA antibody levels, complement C3, C4, immunoglobulin, SLEDAI-2K score, SF-36 score, medication use, and adverse reaction (AEs) records at each follow-up visit time. Measures to strengthen the compliance of research subjects: regularly follow up reminders to the patients.

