## **9.3 Adverse events and serious adverse events**

### **9.3.1 Adverse Event (AE) Definition**

According to ICH-GCP definition

An adverse medical event that occurs in a patient or clinical trial subjects following the use of a drug, but for which there is not necessarily a causal relationship between this medical event and treatment. Thus, an adverse event may be any adverse and unintended sign (including abnormal laboratory findings), symptom, or disease temporally associated with the use of a (study) drug,

regardless of whether it is related to the (study) drug. Currently, mycophenolate mofetil and glucocorticoids are used as first-line drugs in systemic lupus erythematosus. Infection could be considered as the most common AE of both glucocorticoids and immunosuppressants.

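### Protocol 10.3 lists serious adverse events individually only if treatment caused them, and SAP Table 4 has no SAE row, so the planned outputs do not give the all-cause SAE count by arm

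*Combined protocol and SAP*

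**What the plan says.** Protocol 10.3 is the only place that plans an output specific to serious events. It requires individual listing of two groups: AEs that lead to discontinuation of the intervention, with no causal condition, and serious AEs with one: "serious AEs resulting from treatment should be listed individually". For AEs in general, the same section says "AEs are coded and calculated and may be expressed using severity, frequency, and association with the intervention".

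The rules for defining and reporting events have no such filter. Section 9.3.1 defines an AE "regardless of whether it is related to the (study) drug". Section 9.3.2 introduces SAEs as "Adverse medical events at any dose as defined by ICH-GCP" and then lists outcomes only. Section 9.3.6 states: "The investigator will immediately report any SAE to the sponsor, whether or not it is related to the study intervention".

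Section 9.3.4 has all AEs entered on the CRF, with a physician's assessment of severity and of relationship to the investigational product. Section 9.3.3.2 grades relatedness on five levels, from definitely related to unrelated.

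In the SAP, the proportion of patients with AEs is a secondary endpoint (3.2 and 8.6). Table 4 has a row for total AEs and rows for event types such as infections, gastrointestinal events, fractures and osteonecrosis. It has no row for SAEs. SAP section 14 says that AEs are recorded and treated, and adds no analysis.

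**The concern.** Seriousness is defined and reported without regard to cause, but the one output that identifies events as serious depends on cause. A reader of the results would see the SAEs that someone attributed to treatment, and would not know how many others occurred in each arm. The between-arm comparison of all SAEs is the safety comparison that randomization protects. A comparison of attributed SAEs also carries the judgement of whoever made the attribution.

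That matters here because MMF is added in one arm only and there is no placebo (the Brief list in the protocol answers no to placebo). If the person who grades relatedness knows the arm, an event may be attributed more readily in a patient taking an extra immunosuppressant. The listing could then differ between arms when the true rates are the same, or hide a difference that exists.

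**Working it through.** The documents give no SAE rate, so there is no figure of theirs to reproduce. The check is first a comparison of the texts.

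1. **Collection.** All AEs go on the CRF (9.3.4), and both visit schedules (protocol 7.6, SAP 12) have a row for adverse events. There is no causal filter.
2. **Definition and reporting of SAEs.** Neither 9.3.2 nor 9.3.6 has a causal filter.
3. **Totals.** The general AE sentence in 10.3, the secondary endpoint and SAP Table 4 have no causal filter, but none of them separates serious from non-serious events. Presentation by severity is optional in 10.3, and a CTCAE severity grade (9.3.3.1) is not the same as seriousness (9.3.2).
4. **Individual listing.** SAEs are filtered by cause. AEs leading to discontinuation are not.

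An SAE judged unrelated that did not lead to discontinuation is therefore counted in step 3 and identified as serious nowhere.

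Next, is the filter defined, and who applies it?

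- **Cut-off.** None is stated. It is open whether the middle grades of the five-level scale count as caused by treatment.
- **Who judges.** Section 9.3.4 says a physician. Protocol 6.5 says that only assessors were masked. Protocol 7.3 says that masked observers made the regular follow-up assessments. SAP 8.1 gives both patient inclusion and follow-up assessment to the same doctors. None of these assigns the relatedness judgement to a masked person.

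Last, an illustration on assumed inputs. Take n = 65 per arm (protocol 5.3), an equal true proportion r of patients with one SAE, and a proportion a of those SAEs judged related. Assume that none is listed through the discontinuation route. Then patients with an SAE per arm = n × r, listed = n × r × a, and unlisted = n × r × (1 − a).

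| r (assumed) | a, MMF / Control (assumed) | SAE patients per arm | Listed, MMF | Listed, Control | Unlisted, both arms |
|---|---|---|---|---|---|
| 5% | 50% / 50% | 3.25 | 1.6 | 1.6 | 3.25 of 6.5 |
| 5% | 70% / 30% | 3.25 | 2.3 | 1.0 | 3.25 of 6.5 |
| 10% | 50% / 50% | 6.5 | 3.25 | 3.25 | 6.5 of 13 |
| 10% | 70% / 30% | 6.5 | 4.6 | 2.0 | 6.5 of 13 |
| 15% | 50% / 50% | 9.75 | 4.9 | 4.9 | 9.75 of 19.5 |
| 15% | 70% / 30% | 9.75 | 6.8 | 2.9 | 9.75 of 19.5 |

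For example, 65 × 0.10 × 0.70 = 4.55 and 65 × 0.10 × 0.30 = 1.95. The apparent ratio is 0.70 / 0.30 = 2.3 whatever n and r are, so it only restates the assumed attribution. The omission does not need unequal attribution: at 50% in both arms the listing is balanced and half of the SAEs are still missing from it.

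**The case against.** The strongest reply is that this is one loosely worded sentence and that little is lost. Much of that reply stands.

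- **Events do not vanish.** A reader might infer that the causality judgement decides which serious events reach the results at all. It does not. An unrelated serious pneumonia or fracture still has its row in Table 4, and other events fall under the row for other events. What is lost is the label of seriousness.
- **Some unrelated SAEs are listed anyway.** The discontinuation listing in the same sentence has no causal condition. Hospitalization for lupus activity is a severe-flare criterion (SAP 3.1) and so counts in the primary outcome, although not as an SAE.
- **Visit records.** Protocol 7.4 refers to "adverse reaction (AEs) records at each follow-up visit time", and 7.1.4 uses the same term. A reader might infer that only suspected reactions are collected. The parenthesis equates the term with AEs, and 7.6, 9.3.4 and SAP 12 record all of them, so this is loose wording.
- **Masking.** A reader might infer that the judging physician knows the arm. That is reasonable in a trial without placebo, but it is not stated, and 7.3 describes masked observers.
- **Control arm.** A reader might infer that a Control event cannot be attributed to treatment. Section 10.3 says treatment, not MMF, and Control patients take HCQ and prednisone. Section 9.3.1 names infection as the most common AE of glucocorticoids as well as of immunosuppressants.

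It may also be that the authors meant treatment-emergent events. The text does not say so, and the same edit would settle it.

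None of this supplies an all-cause SAE count by arm.

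**Conclusion.** The point holds in limited form. Protocol 10.3 makes the individual listing of SAEs depend on causality, against the all-cause basis of 9.3.2 and 9.3.6, and no SAP table supplies the missing count. Except where the event led to discontinuation, an SAE judged unrelated is counted as an AE but not shown as serious. This follows from the texts alone and needs no assumption.

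That the filter acts differently in the two arms is a possibility, not a finding. It rests on the absence of a placebo, on the lack of any stated masked judge, and on the undefined cut-off. Its size cannot be derived: the SAE rates and attribution rates in the working are all assumed, and the imbalance ranges from none under equal attribution to 2.3-fold at 70% against 30%. The primary outcome is not affected. The underlying data should exist, because every SAE goes to the sponsor, so this is a gap in planned reporting and not in collection.

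**What to change.** In protocol 10.3, delete the three-word causal qualifier on serious AEs, and list every SAE by arm with its relatedness grade as a column. In SAP Table 4, add a row for patients with at least one SAE regardless of attribution. These two changes restore the all-cause count and leave the relatedness information in view.

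It would also help to state who grades relatedness and whether that person is masked. Once relatedness is only a column, no cut-off is needed for the listing.

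Replacing adverse reaction by adverse event in 7.1.4 and 7.4 is a tidy-up. Rows in Table 4 for CTCAE grade 3 to 5 events and for AEs leading to discontinuation are optional.

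The cost is one edited sentence, one table row and a slightly longer listing. No new data are needed: AEs, severity and relationship are already on the CRF (9.3.4), and every SAE is already reported (9.3.6).

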## **10.4 Baseline Descriptive Analysis**

Descriptive statistics were used to compare demographic characteristics and laboratory indicators between the groups at baseline.

## **10.5 Subgroup analysis**

/

# **11. Supporting Documents and Notices**

## **11.1 Informed Consent Process**

Informed consent should be completed before the subject agrees to participate in the research and should continue throughout the research. The informed consent form was approved by the ethics committee, and the research subjects should read the informed consent form. The investigator will explain the research process and answer questions from the subject; and inform the subject of the possible risks and their rights. Subjects may discuss this with their families or guardians prior to consenting to participate.

The investigator must inform the subject that participation in the research is voluntary and that they may withdraw from the follow-up at any time during the trial. A copy of the informed consent form can be provided to the research subjects for preservation. The rights and welfare of

the research subjects will be protected and it is emphasized that the quality of their medical care will not be compromised by refusal to participate in the study.

### **11.2 Research Termination and Closure**

Listing possible reasons for research discontinuation or suspension (unintended risks, failure to execute the study plan, quality of data and so on). In case of research suspension or moratorium, the person in charge should promptly notify the research subjects and report to the Ethics Committee and the Science and Technology Development Office. If the reasons for study discontinuation or suspension are resolved, the study can be resumed.

### **11.3 Privacy protection**

This research involves the application of a dedicated person for the collection of specimens that need to be collected, and a dedicated person for the collection and storage of follow-up data. Only the research sponsor and relevant research personnel have access to the information, and any research information cannot be disclosed to unauthorized third parties without prior approved consent.

### **11.4 Collection and use of specimens and data**

Only collected specimens and data for this study.

### **11.5 Quality Control and Quality Assurance**

- 1) The physicians, nurses, doctoral students, clinical trial observation and other staff involved in this trial must have professional clinical knowledge as required in the trial protocol.
- 2) The investigator and other staff involved in the trial should perform their duties and strictly follow the clinical trial protocol and adopt standard operating procedures to ensure the implementation of the quality control and quality assurance system of the trial. The investigator and other staff involved in the study have obtained GCP certificate and have experience to control the quality of the study.
- 3) All observations and findings in clinical trials should be verified. Quality control must be performed at each stage of data processing to ensure the integrity, accuracy, authenticity and reliability of the data.
- 4) The investigator and other staff involved in the research had sufficient time to conduct the trial and a reliable source of subjects.
- 5) All items involving imaging and laboratory tests should comply with national standards.
- 6) This trial involves specimens that need to be collected should be collected by a dedicated person, and follow-up data should be collected and kept by a dedicated person.
- 7) The test procedures should be performed according to standard procedures.
- 8) When the research protocol needs to be modified, an ethics committee should be convened to give full play to the functions of the ethics committee and to ensure that the interests of the subjects are protected.
- 9) Save all the original data according to the requirements in the plan, in order of time for verification.
- 10) The contract research organization must assign supervisors who have been trained in this trial. The inspector must have a relevant professional background in medical pharmacology and strictly follow the standard process to verify the project.

11) The auditors systematically check the activities and documents related to the clinical trial to evaluate whether the trial is conducted in accordance with the trial protocol and standard operating procedures and relevant regulations, and whether the experimental data are timely, true, accurate and full record. The audit should be performed by personnel who are not involved in the clinical trial.

12) Audits are established to ensure that clinical trials are conducted in a manner consistent with standard operating procedures and relevant regulations.

13) Regular audits and meetings with relevant personnel to discuss issues found during audits.

## **11.6 Data processing and record keeping**

### **11.6 Data collection and management**

The types of source data to be collected in this trial are: medical records, AEs, questionnaires, laboratory results and so on. Data collection will be performed by clinical research staff under the supervision of the person in charge, who will be responsible for the accuracy, completeness, and timeliness of the reported data. All data should be clear to ensure accurate interpretation and to ensure their traceability. Clinical data will be maintained in a database, which should be password protected, and a logical proofreading process should be established when the database is created.

## **11.7 Publishing and Data Sharing Agreements**

Data for all subjects included in the article, the research protocol and statistical analysis plan are available upon publication of the relevant results by sending an email inquiry to the research PI and obtaining consent from the research PI.

## **11.8 Conflict of Interest Statement**

None

## **12 Appendix**

### **12.1 Workflow of glucocorticoids decrease process from baseline to week 96**

In this trial, we randomly assigned patients (1:1) to Control group and MMF group. The Control group received treatment with HCQ (5mg/kg/day) and prednisone (0.5mg/kg/day); while MMF group received treatment with HCQ (5mg/kg/day) and prednisone (0.5mg/kg/day) plus MMF 500mg twice daily. The dose of MMF stayed the same unless a contrary or severe adverse event occurred.

Prednisone dose was tapered as follows:

Initial dose (0.5mg/kg/day) maintained for four weeks

↓  
tapered 5mg every two weeks till to 20 mg/day

↓  
tapered 5mg every month

↓  
gradually to 0.1-0.2mg/kg/day

The taper of prednisone doses was determined by the physicians according to the assessment of

patients.

